‘Overall how satisfied are you with the results of your hip replacement surgery?’‘How satisfied are you with the results of your hip replacement surgery for improving your ability to do housework or yard work (such as cooking, cleaning, or gardening and raking leaves)?’‘How satisfied are you with the results of your hip replacement surgery for improving your ability to do recreational activities (such as taking walks, swimming, bicycling, playing golf, dancing, going out with friends)?’‘How satisfied are you with the results of your hip replacement surgery for relieving your pain?’

The response to each question will be recorded using a 4-point Likert scale: very satisfied, somewhat satisfied, somewhat dissatisfied and very dissatisfied. These questions and the 4-point Likert assessment have been validated and demonstrated to be reliable to measure satisfaction following primary hip replacement surgery [23]. Change in pain, stiffness, and functional ability from baseline to 3, 6 and 12 months following surgery will be assessed using the subscales of the WOMAC [18] questionnaire. Change in patient-reported quality of life from baseline to 3, 6 and 12 months following knee replacement surgery will be assessed using the EQ-5D-3L general health questionnaire [28] which evaluates five domains (-5D), which include mobility, self-care, usual activities, pain/discomfort and anxiety/depression. This is a two page questionnaire that consists of five dimensions, with the responses recorded at three levels (3L) of severity (no problems, some problems or extreme problems). The second page consists of a standard vertical 20cm visual analogue scale (EQ-5D VAS) which is transformed to a scale of 0 to 100 measuring current health-related quality of life. Each patient’s health state, derived from the EQ-5D, will be measured before and after their surgery to determine the change in their health gain or loss after their knee replacement surgery. The health state will then be multiplied by the time spent in that state to derive the QALYs gained or lost. The cost per QALY will then be calculated by dividing the cost of the procedure by the QALYs gained after TKR.

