An economic evaluation will be conducted from an NHS perspective. Data collection from the study will also focus on estimating the cost of the interventions and subsequent use of services. Analyses will be carried out from an NHS perspective and will include the capture of resource use from secondary and primary/community care. All relevant costs associated with providing the interventions will be included including length of stay. All unit costs will be derived using routine data sources and study specific estimates. Costs in the follow-up period will include use of secondary care services, e.g. inpatient stays and outpatient visits, and primary/community care services, e.g. general practice visits, district nurse visits and prescription costs incurred over the follow-up period. This data will be collected using a health service utilisation patient diary. Data on use of services will be combined with appropriate unit costs to produce a cost for each trial participant. From these, a mean cost per intervention will be calculated. Health-related quality of life will be measured using EQ-5D-3L which is a very simple measure which patients complete at the start and end of treatment. It comprises five dimensions of health: mobility, ability to self-care, ability to undertake usual activities, pain and discomfort, and anxiety and depression. The cost-effectiveness analysis of the two types of surgery will be based on incremental cost of a quality-adjusted life year (QALY). QALYs will be estimated using the area under the curve approach. The results will be presented as point estimates of mean incremental costs and QALYs. The results of the analyses will include deterministic and stochastic sensitivity analysis, presented as point estimates and cost-effectiveness acceptability curves (CEACs).

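### The protocol gives two unreconciled rules for cost per QALY, and the one under Outcome measures, procedure cost over before-after QALY gain, does not compare the two operations

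*Protocol article*

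**What the plan says.** The Objectives section lists, among the secondary aims, a comparison of the cost-effectiveness of the two interventions from the NHS perspective.

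Two places then say how cost per QALY is obtained.

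- **Outcome measures, end of the EQ-5D description.** Each patient's health state "will be measured before and after their surgery to determine the change in their health gain or loss after their knee replacement surgery". Next, "The health state will then be multiplied by the time spent in that state to derive the QALYs gained or lost". Finally, "The cost per QALY will then be calculated by dividing the cost of the procedure by the QALYs gained after TKR".
- **Statistical analysis, economic evaluation.** "The cost-effectiveness analysis of the two types of surgery will be based on incremental cost of a quality-adjusted life year (QALY"). It adds that "QALYs will be estimated using the area under the curve approach" and that "The results will be presented as point estimates of mean incremental costs and QALYs". Costs there cover the intervention, length of stay, and later secondary, primary and community care. Sensitivity analyses and acceptability curves are also planned.

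The paragraph after the division rule, still under Outcome measures, sets the horizons: 12 months, then projections to 5 years, 10 years and lifetime. It also describes collection of resource use at 3, 6, 9 and 12 months.

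On timing, the Statistical analysis section calls the EQ-5D "a very simple measure which patients complete at the start and end of treatment". The Objectives and Outcome measures sections schedule it at baseline and at 3, 6 and 12 months.

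**The concern.** The two rules define different quantities. The first asks what one operation costs per QALY relative to the patient's state before surgery. The second asks what the robot and sensor cost per QALY that they add to a manual replacement. Only the second matches the objective.

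Both arms receive the same implant, and all patients have the same rehabilitation. Much of the before-after gain is therefore likely to be benefit that any knee replacement would give. A ratio with that shared gain in its denominator responds weakly to what the technology adds.

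The article does not call the first ratio descriptive and does not rank the two rules. The Dissemination policy expects several papers on secondary outcomes, and the Discussion promises a statement on economic viability in the NHS. As written, either ratio could be reported as the protocol-specified cost per QALY, and the two can point to different conclusions.

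**Working it through.** **No figure to reproduce.** The documents give no cost, utility or cost-effectiveness result. The check is therefore algebra, followed by an illustration on assumed inputs.

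**The two rules side by side**

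| | Outcome measures | Statistical analysis |
|---|---|---|
| Reference | patient's own state before surgery | the other arm |
| Cost | procedure only | intervention, length of stay, follow-up NHS care |
| QALYs | health state × time, as gain or loss | area under the curve |
| Result | one ratio per operation | incremental cost per QALY |

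The QALY row is the smallest difference, since area under the curve is itself health state multiplied by time. The reference and the cost scope are what separate the rules.

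**Formulae.** Let C be the manual cost, G the manual QALY gain over baseline, dC the extra robotic cost and dQ the extra robotic QALYs.

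- Average ratio, manual arm: C / G
- Average ratio, robotic arm: (C + dC) / (G + dQ)
- Incremental ratio: dC / dQ

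The robotic average ratio is a weighted mean of the manual average ratio (weight G) and the incremental ratio (weight dQ). When dQ is small beside G, the shared benefit dominates and the incremental signal is damped.

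**Assumed inputs, none from the documents.** C = 6,000, G = 0.25, dC = 1,500, and dQ varied. Follow-up costs are taken as equal between arms, so the procedure cost difference is also the total cost difference. The same dQ enters both rules. The manual average ratio is 6,000 / 0.25 = 24,000.

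| dQ | Robotic average ratio | Incremental ratio |
|---|---|---|
| 0.10 | 7,500 / 0.35 = 21,429 | 1,500 / 0.10 = 15,000 |
| 0.05 | 7,500 / 0.30 = 25,000 | 1,500 / 0.05 = 30,000 |
| 0.02 | 7,500 / 0.27 = 27,778 | 1,500 / 0.02 = 75,000 |
| 0.01 | 7,500 / 0.26 = 28,846 | 1,500 / 0.01 = 150,000 |
| −0.01 | 7,500 / 0.24 = 31,250 | dominated: dearer and less effective |

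Check of the weighted mean at dQ = 0.01: (0.25 × 24,000 + 0.01 × 150,000) / 0.26 = 7,500 / 0.26 = 28,846.

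Over the four positive values the average ratio changes by a factor of about 1.35 (28,846 / 21,429), and the incremental ratio by a factor of 10 (150,000 / 15,000). The error has no fixed direction: at 0.10 the average ratio is above the incremental one, and at 0.05 and below it is under it. In the last row the robotic arm is worse on both counts, yet its average ratio still looks like an ordinary cost per QALY.

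**The case against.** The strongest reply is that the comparative analysis is already specified. The Statistical analysis section has incremental costs and QALYs, area under the curve, full NHS costs and acceptability curves. The division sentence merely closes a description of the EQ-5D, does not mention the arms, and could sit beside an incremental result as a per-procedure summary. This largely stands. A reader might infer that the trial cannot say whether the robotic approach is cost-effective, or that follow-up costs are left out of the evaluation. The documents do not support either reading: the incremental analysis is planned, and the costs missing from that one sentence are collected and counted elsewhere. What the reply does not supply is any wording that makes the sentence descriptive or subordinate.

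A reader might also infer from the start-and-end phrase that the 3- and 6-month EQ-5D data would be discarded. That is not supported either. The phrase is a loose description of the instrument, the four-point schedule is clear, and the same section requires area under the curve.

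It is also fair to say that 150,000 is one extreme point. At an extra gain of 0.05 QALY the two ratios are 25,000 and 30,000, which is a modest gap. The range matters more than any single row.

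**Conclusion.** The point holds as a conflict between two stated rules. The Outcome measures rule is wrong as written for the comparative objective, and the Statistical analysis rule is suitable. The economic question can be answered if the latter governs, but the article does not say that it does.

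That the two ratios differ in kind follows from the algebra and needs no assumption. The size does: it rests on the assumed costs and gains, on equal follow-up costs between arms, and on no willingness-to-pay threshold, since the documents give none. On those inputs the gap runs from modest to very large, and the average ratio fails to show dominance.

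Only a secondary outcome is affected. The primary WOMAC comparison and the data collection are untouched. The EQ-5D timing phrase is a wording note and no more.

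**What to change.** 1. Under Outcome measures, delete the sentence that divides procedure cost by QALYs gained, or label it as descriptive only and not used to compare the arms.
2. State once that the rule in the Statistical analysis section governs at every horizon planned (12 months, 5 years, 10 years and lifetime): difference in mean total NHS cost between arms divided by difference in mean QALYs between arms. A rule limited to 12 months would conflict with the planned projections.
3. State that within-trial QALYs come from the area under the curve through EQ-5D at baseline, 3, 6 and 12 months.
4. As a wording note, bring the start-and-end phrase in the Statistical analysis section into line with that schedule.

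Adjustment of the QALY difference for baseline utility can be left to the analysis plan.

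The cost is a few lines of protocol text. The EQ-5D and resource-use data needed are already scheduled, and neither the sample size nor the visits change.

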### Defined end of trial

The end of trial is the date of the 12-month follow-up visit of the last participant. Each participant has the right to withdraw from the study at any time. In addition, the investigator may discontinue a participant from the study at any time if the investigator considers it necessary for any reason including ineligibility (either arising during the study or retrospective having been overlooked at screening); significant protocol deviation, i.e. intervention not used as intended at time of surgery; significant non-compliance with treatment regimen or study requirements; an adverse event which requires discontinuation of the study medication or results in inability to continue to comply with study procedures; consent withdrawn; or lost to follow-up.

Participants who wish to withdraw consent for the trial or whose participation from the trial is discontinued will have anonymised data collected up to the point of that withdrawal of consent included in the analyses unless the participant specifically asks for all data collected to be destroyed. No additional data will be collected from the participant. The reason for withdrawal will be recorded in the CRF. Participants who withdraw once they have been randomised will not be replaced. If the participant is withdrawn due to an adverse event, the investigator will arrange for follow-up visits or telephone calls until the adverse event has resolved or stabilised.

At the end of the trial, patient will resume standard practice of care of the study centre in place at that time for follow-up of routine TKR.

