**Serious**	SAE	SADE	
		Anticipated	Unanticipated
		ASADE	USADE

**Table 2 Tab2:** Device deficiency category according to SADE

Device deficiency	Could lead to a SADE	Would not lead to a SADE
**Category:**	Device deficiency with SADE potential	Device deficiency without SADE potential

**Table 3 Tab3:** Classification criteria for the intensity of the adverse event

Intensity	Description
Mild	An event easily tolerated by the patient, causing minimal discomfort and not interfering with everyday activities
Moderate	An event sufficiently discomforting to interfere with normal everyday activities
Severe	An event that prevents normal everyday activities

The expectedness of the AE will be assessed by the CI or an appropriately trained designee using the list of expected events below. This list is based on current clinical knowledge of expected intra- and post-operative complications of TKR. Intra-operative complications: not able to proceed with expected implant (in this case triathlon TKR), soft tissue damage, neurovascular damage, fracture, patients becomes medically unwell and cannot perform TKR, blood loss and general medical complications, e.g. heart attack, stroke. Post-operative complications: infection (superficial and deep implant infection), deep vein thrombosis and pulmonary embolus, stiffness, swelling, numbness, neurovascular complications, wound breakdown, fracture and general health problems, e.g. stroke, heart attack, kidney failure and potential loss of limb and life.

The relationship between the investigational medical device (including comparator treatments) and the occurrence of each AE must be assessed and categorised by the Chief Investigator (or delegate). Related events are those that are related to the administration of the medical device or study procedures. Each AE will be categorised as (1) not related (no relationship with the investigational device; other factor(s) certainly or probably causative) or (2) possibly related (the nature of the event, underlying medical condition, concomitant medication or temporal relationship make it possible that the AE has a causal relationship to the device).

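### Stopping data collection when the intervention was not used as intended at surgery can create missing primary outcomes related to the robotic arm

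*Protocol article*

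**What the plan says.** All the operative text is in the protocol article under Defined end of trial.

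- **Who decides:** "the investigator may discontinue a participant from the study at any time if the investigator considers it necessary for any reason".
- **Grounds:** the list of reasons includes "significant protocol deviation, i.e. intervention not used as intended at time of surgery" and "ineligibility (either arising during the study or retrospective having been overlooked at screening". Withdrawal of consent and loss to follow-up stand in the same list.
- **Consequence:** the rule on data covers "Participants who wish to withdraw consent for the trial or whose participation from the trial is discontinued". These people "will have anonymised data collected up to the point of that withdrawal of consent included in the analyses", unless they ask for their data to be destroyed. After that, "No additional data will be collected from the participant".
- **Replacement:** "Participants who withdraw once they have been randomised will not be replaced".
- **Exception:** a participant withdrawn because of an adverse event is followed until that event has resolved or stabilised.

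Elsewhere, Trial design and Allocation use the term intervention group for the robot-and-sensor arm. Allocation also says that treatment cannot be concealed from patients or clinicians. Objectives and Outcome measures put the primary outcome, change in WOMAC function, at 6 months. Nothing in the article says that a patient with a surgical deviation stays in follow-up.

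**The concern.** The paragraph treats two different events as one: departure from the allocated procedure, and the end of a patient's participation in data collection. Only withdrawal of consent requires the second.

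A deviation in how the operation was done is known on the day of surgery. If the patient is discontinued on that ground, the 6-month WOMAC is never collected, nor are later EQ-5D and resource-use data for the cost-utility analysis. Robot and sensor failures, such as an abandoned registration, a conversion to jigs or a sensor left out, have no counterpart in the manual arm. The ground for stopping is therefore linked to arm, and the decision is discretionary in a trial where clinicians know the allocation. If the affected patients do worse than the other robotic patients, leaving them out flatters the robotic arm in a comparison that Trial design describes as one of effectiveness.

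**Working it through.** **1. The plan's own figure.** Inputs from Sample size: difference 15, SD 26.5, one-sided alpha 0.05, power 80%.

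- Normal approximation: n per arm = 2 × (1.645 + 0.842)² × 26.5² / 15² = 38.6, so 39.
- Noncentral t: 40 per arm, 80 in total, as stated.
- With 10% loss: 80 / 0.9 = 88.9, so 89, stated as 90 (45 per arm).

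The figure reproduces. The concern does not depend on it, but it sets the scale.

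**2. Which data are lost.** For a patient discontinued at surgery because the robot or sensor was not used as intended:

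| Data | Status under the rule |
|---|---|
| Baseline questionnaires and gait | kept |
| Surgical and inpatient data | kept up to discontinuation |
| Adverse event that led to withdrawal | followed until resolved or stable |
| 6-month WOMAC function (primary) | not collected |
| WOMAC, OKS, FJS and EQ-5D at 3, 6 and 12 months | not collected |
| Resource use after discharge | not collected |

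**3. Bias.** Let f be the share of the robotic arm removed, and D the number of points by which those patients would do worse than the rest of that arm, whose mean is R. The full-arm mean is (1 − f)R + f(R − D) = R − fD. Dropping the removed patients gives R, so the bias towards the robotic arm is f × D.

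Neither f nor D is in the document. Assume that 2 to 4 of 45 are removed and D is 0 to 20 points:

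- D = 0: bias 0.
- (2/45) × 10 = 0.44 points.
- (4/45) × 20 = 1.78 points, which is 1.78 / 15 = 12% of the target difference.

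**4. Bias against sampling error.** With 40 per arm, SE = 26.5 × √(2/40) = 5.93. The two non-zero results are 0.44 / 5.93 = 0.07 SE and 1.78 / 5.93 = 0.30 SE.

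**5. Numbers and power.** If these removals come on top of 10% other loss, 45 × 0.9 × (41/45) = 36.9, so about 37 in the robotic arm.

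- 40 and 40: power = Φ(15/5.93 − 1.645) = 0.81.
- 40 and 37: SE = 26.5 × √(1/40 + 1/37) = 6.04; power = Φ(15/6.04 − 1.645) = 0.80.

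**6. Wider assumptions.** Taking f from 5% to 20% and D from 10 to 26.5 gives a bias of 0.5 to 5.3 points. If the gap is present even when the treatment has no effect, one-sided type I error is 0.059 to 0.211 (f = 10%, D = 15: bias 1.5, error 0.081). The top of this range needs a fifth of the robotic arm to be removed, more than twice 4/45.

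**The case against.** Several stronger readings are tempting, and the document does not support them.

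- **That failures will be removed, and from one arm only.** The rule says the investigator may discontinue, so removal is possible and not automatic. The term intervention is also not used consistently: Objectives speaks of two interventions and Statistical analysis of two intervention arms. A significant deviation could in principle occur in a manual case. What stands is narrower: non-use of the robot or sensor can happen only in the robotic arm.
- **That retrospective ineligibility is also one-sided.** It is not. Eligibility is settled before randomisation, so errors found later can fall in either arm. It has the same consequence for data but no built-in direction.
- **That the expected-events list under Safety reporting confirms the problem.** The entry "not able to proceed with expected implant (in this case triathlon TKR" applies to both arms, since all participants are to receive that implant, and it says nothing about discontinuation.
- **That complications are biased in general.** Surgical and inpatient data are kept, and an adverse event that led to withdrawal is followed. The loss lies in later questionnaires and later resource use.
- **That losses will exceed the planned 10%.** Sample size takes the 10% from earlier arthroplasty studies at the institution and does not say whether discontinuations were counted in it.

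The most substantial objection concerns D. A robotic case converted to jigs receives the control operation with the same implant and approach. If the treatments do not differ and the conversion does no harm, D is zero, there is no bias and only a little power is lost. Type I error rises only if the removed patients do worse for some other reason, for example because theirs were the difficult knees. That is plausible, but the document gives no figure for it.

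It may also be said that analysis sets belong to an analysis plan that is not shown. That is fair for the choice of set. It does not answer the point, because no plan can recover outcomes that the protocol says are not to be collected.

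**Conclusion.** The concern holds in a limited form. As written, a clinician who knows the allocation can, at discretion, end data collection for a randomised patient because of how the operation was done, and one such ground can arise only in the robotic arm. The result is potential arm-related missingness in the primary outcome and in the later economic data, and no other part of the article offsets it.

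The size cannot be determined from the document. Under the assumptions of 2 to 4 removals in 45 and a gap of 0 to 20 points, the bias is 0 to about 1.8 points (at most 0.30 SE). The power cost is about one percentage point if the removals add to the 10% allowance. This is modest beside a 15-point target, and it could be nil. The case for changing the rule rests less on the expected size than on three facts: the possible bias favours the new treatment, the lost data cannot be recovered, and prevention is cheap.

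**What to change.** In Defined end of trial:

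1. Remove deviation in the use of the intervention at surgery, and ineligibility found later, as reasons to stop data collection.
2. State that outcomes continue to be collected at 3, 6 and 12 months from every randomised participant who has not withdrawn consent, whichever operation was performed.
3. State that these participants stay in their allocated arm for the primary comparison.
4. Record each deviation and its reason, for use in a sensitivity analysis.

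The cost is one paragraph and further questionnaires for a few patients. The 3- and 12-month contacts coincide with routine clinics. The 6-month contact, which carries the primary outcome, does not: Trial design describes it as postal and Recruitment as a research visit, but it is an extra contact either way and should be budgeted for. The planned 90 patients need not change.
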